## 10. Sample Size Estimation

The primary outcome measure is Royal Brisbane Hospital Outcome Measure for Swallowing (RBHOMS), which is a 10-point ordinal scale that ranges over four stages of oral intake from stage “A” (nil by mouth) to “D” (maintaining oral intake). The sample size is estimated to compare the proportion of those who are rated at stage “D.” Based on our previous clinical study [23], we estimate that 60 participants in each group will be needed to detect 20% difference of the proportion between the treatment and control group with a false positive error of 5% and power of 80%. To compensate for dropouts during treatment period, we inflate this value by 15% and hence a total of 140 patients will be recruited, with 70 each in the treatment and control group.

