## 8. Primary Outcome

Royal Brisbane Hospital Outcome Measure for Swallowing (RBHOMS) is a valid bedside scale for monitoring difficulties in daily swallowing function based on clinical indicators of swallowing, but not on texture-modified diets [20]. RBHOMS is a 10-point ordinal scale that ranges over four stages of oral intake: stage A, nil by mouth (levels 1–3); stage B, commencing oral intake (level 4); stage C, establishing oral intake (levels 5–7), and stage D, maintaining oral (levels 8–10). Both acupuncture group and nonacupuncture control group patient will be conducted three times RBHOMS, with one being conducted at baseline, one at the end of treatment (2 months after inclusion), and the last one at the end of follow-up period (2 months after treatment completion). All RBHOMS will be conducted by a registered speech therapist blinded to group allocation.

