## 11. Data Analysis

All analyses will be conducted according to the intention-to-treat principle. Descriptive statistics will be computed for each of the analyzed variables. For the primary outcome, chi square test will be used. All continuous variables such as swallowing time, swallow quality-of-life, and BMI will be analyzed using *t*-test where appropriate. Swallow function scores will be analyzed using Mann–Whitney *U* test. The possible relationship between some baseline data and main outcomes will be explored using multivariable analysis. All statistical tests will be two-sided, and *p* < 0.05 is considered statistically significant. The statistical software of SPSS (SPSS, SPSS Inc., Chicago, USA) version 20 will be used for the analysis.

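### The primary test drops baseline RBHOMS in a non-randomised comparison and reduces a 10-level ordinal scale to stage D yes/no

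*Protocol article*

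**What the plan says.** - Section 8 (Primary Outcome): "RBHOMS is a 10-point ordinal scale that ranges over four stages of oral intake". The top stage is "stage D, maintaining oral (levels 8–10"). The scale is scored at baseline, at the end of treatment and at the end of follow-up. Neither later assessment is named as primary.
- Section 10 (Sample Size Estimation): "The sample size is estimated to compare the proportion of those who are rated at stage" D. The target is to "detect 20% difference of the proportion between the treatment and control group" "with a false positive error of 5% and power of 80"%. On the source: "Based on our previous clinical study [23], we estimate that 60 participants in each group will be needed". No control-arm rate is printed.
- Section 11 (Data Analysis): "For the primary outcome, chi square test will be used". The variable entering the test is not named; stage D yes/no follows from Section 10. For the 7-point secondary scale, "Swallow function scores will be analyzed using Mann–Whitney" is the rule.
- Baseline data appear twice: in an exploratory multivariable analysis (Section 11), and in an adjustment to be settled later, with no model or covariate list (Section 12).
- Section 3.3 admits RBHOMS scores from 2 to 8. Sections 3.1 and 5 place willing patients in the acupuncture arm and unwilling ones in the control arm.

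**The concern.** Two weaknesses meet in the primary test.

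**Baseline severity is left out.** The arms are formed by patient preference, so nothing in the design balances starting RBHOMS. The stage D proportion after treatment depends heavily on where patients started, and someone entering at level 8 meets the endpoint before any treatment. If one arm enrols milder patients, an unadjusted comparison reports that as a treatment effect, or hides a real one.

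**Ten ordered levels become two.** A move from level 2 to level 7 counts as failure and a move from 7 to 8 as success. If the chi-square were instead run on all ten levels, it would ignore their order and have sparse cells at 60–70 per arm. The plan accepts a rank method for its other ordinal swallowing scale and gives no reason for treating the primary scale differently.

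At stake are the validity of the main comparison as far as measured severity goes, and some power.

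**Working it through.** **Inputs.** From the protocol: 60 evaluable per arm, a 20-point difference read as absolute, two-sided 5%, 80% power, ten levels, stage D = levels 8–10. Assumed: the control stage D rate p₁ (not stated, so varied), a logistic spread over the ten levels (two spreads tried) and a proportional-odds effect.

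**1. The plan's own figure.** With p₂ = p₁ + 0.20 and p̄ their mean,

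n = [1.96√(2p̄(1−p̄)) + 0.8416√(p₁(1−p₁) + p₂(1−p₂))]² / 0.20².

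- p₁ = 0.09: (1.0874 + 0.4515)²/0.04 = 59.2, so 60 per arm.
- p₁ = 0.30: (1.3579 + 0.5708)²/0.04 = 93.0, so 93 per arm.

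The stated 60 is reproduced at control rates of about 9–10% or 70–71%. Between 15% and 65% the formula asks for 73–97 per arm, and 60 per arm gives 59–72% power. Without the control rate, one cannot tell which case applies.

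**2. What the stage D cut costs under proportional odds.** The odds ratio is set by the same 20-point difference. Whitehead's formula is

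n = (1.96 + 0.8416)² / [(ln OR)² × V], with V = (1 − Σp̄ₖ³)/6, where p̄ₖ is the mean of the two arms' probabilities at level k.

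Example at p₁ = 0.30: OR = (0.5/0.5)/(0.3/0.7) = 2.33; ln OR = 0.847; Σp̄ₖ³ = 0.016; V = 0.164; n = 7.849/(0.718 × 0.164) = 66.7, so 67. Efficiency of the cut is 67/93 = 72%. Power at 60 per arm is Φ(0.847 × √(60 × 0.164) − 1.96) = Φ(0.70) = 76% for the ordinal test. For chi-square it is Φ((0.20√60 − 1.358)/0.678) = Φ(0.28) = 61%.

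| Control rate | n per arm, chi-square | n per arm, ordinal | Efficiency of the cut | Power at 60, chi-square | Power at 60, ordinal |
|---|---|---|---|---|---|
| 10% | 62 | 27 | 44% | 79% | 99% |
| 20% | 82 | 50 | 61% | 67% | 87% |
| 30% | 93 | 67–68 | 72–73% | 61% | 76% |
| 40% | 97 | 74 | 76% | 59% | 72% |
| 50% | 93 | 68–70 | 73–75% | 61% | 74–75% |
| 60% | 82 | 52–56 | 63–68% | 67% | 83–86% |

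The formula gives a gap of 12–20 points. Simulation with another assumed spread gave 69% against 62% at a 40% control rate, so the lower end is about 7 points.

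**3. The same 20 points, with benefit only from stage C into D.** Simulated power at 60 per arm, control rates 10/20/30/40%: chi-square 79/69/60/60%, Mann–Whitney 27/30/32/35%. The ranking reverses.

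**4. Baseline imbalance with no treatment effect.** In an illustrative simulation with baseline severity differing by 0.4 SD between arms, the unadjusted test rejected in 16% of trials and the baseline-adjusted test in 5%. The 0.4 SD is an assumption; the protocol gives no figure.

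**5. Precision from baseline.** With a baseline correlation of 0.5 and control rates of 30–50%, rank ANCOVA reached 84–87% power against about 62% for chi-square. That comparison changes two things at once. Keeping stage D but adjusting for a strongly prognostic baseline (latent slope 1.5) gave about 79/77/74% against 67/63/61% at control rates of 20/30/40%, so a good part of the gain comes from baseline and not from the ordinal scale.

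**The case against.** Stage D is one of the scale's own named stages, not a cut invented for the trial, and a responder proportion is easy to read. Sections 10 and 11 fit together: a proportion, tested by chi-square. The functional oral intake scale gets a rank test and could show shifts among severe patients. The ordinal advantage rests on a shift across levels, which nothing in the protocol establishes, and step 3 shows it can reverse. The study calls itself a pilot and already names lack of randomisation as its main limitation.

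Much of this stands. It makes the ordinal primary a preference that depends on an assumption, and it rules out three stronger readings:

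- *That most of the information is thrown away.* At control rates of 20–60% the loss is 24–39%; of the rates tabulated, only 10% takes it above half.
- *That the trial is short of power.* The control rate rests on a cited study and is not printed. Near 9–10% or 70–71%, the stated 80% holds.
- *That baseline RBHOMS goes unused.* Sections 11 and 12 foresee exploratory and later adjustment, although neither names RBHOMS.

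The objection does not answer the baseline point. Self-selected arms and entry at a level that already counts as success make an unadjusted primary test hard to defend, and acknowledging non-randomisation does not repair it.

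**Conclusion.** The point holds in two parts of different strength.

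**Firm:** the primary test should include baseline RBHOMS. This follows from the allocation rule, the overlap between the entry range and stage D, and the fact that the score is already collected. Adjustment deals with measured baseline severity only; other differences between willing and unwilling patients remain.

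**Conditional:** analysing the ordered levels is more efficient if the effect shifts patients across the scale. The cut then costs about a quarter to two fifths of the information at assumed control rates of 20–60% (56% at 10%), or roughly 7–20 points of power at 60 per arm. If benefit is confined to the boundary between stages C and D, the gain disappears or reverses. No shortfall against the planned 80% is claimed.

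**What to change.** 1. Name one primary time point and the exact variable tested, and print the control-arm stage D rate behind the 60 per group.
2. Replace the unadjusted chi-square with a model that includes baseline RBHOMS. Preferred: proportional-odds regression on the RBHOMS level, reporting the common odds ratio with 95% CI.
3. Report the stage D proportion as supportive, also adjusted for baseline RBHOMS by logistic regression.
4. If the team prefers to keep stage D as primary, the minimum is logistic regression for stage D adjusted for baseline RBHOMS, with a sentence saying why the responder definition was chosen.

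The cost is a change of wording and of analysis code; no new patients, visits or measurements are needed. The downsides are that an odds ratio is less direct than a percentage, which is why both should be shown, and that the ordinal gain depends on a shift across levels. The choice should be fixed before outcome data are seen.

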## 11. Data Analysis

All analyses will be conducted according to the intention-to-treat principle. Descriptive statistics will be computed for each of the analyzed variables. For the primary outcome, chi square test will be used. All continuous variables such as swallowing time, swallow quality-of-life, and BMI will be analyzed using *t*-test where appropriate. Swallow function scores will be analyzed using Mann–Whitney *U* test. The possible relationship between some baseline data and main outcomes will be explored using multivariable analysis. All statistical tests will be two-sided, and *p* < 0.05 is considered statistically significant. The statistical software of SPSS (SPSS, SPSS Inc., Chicago, USA) version 20 will be used for the analysis.

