## 2. Objective

This study is to evaluate the effectiveness and safety of acupuncture for the treatment of dysphagia as a complication of stroke.

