## 5. Intervention

Patients in both acupuncture and no-acupuncture control group will receive the conventional supportive and rehabilitative treatment, such as swallowing therapy programmes, nonoral feeding, medications, and physical stimulation [8, 9]. On top of the supportive treatment, patients in the acupuncture group will receive real acupuncture treatment, while patients assigned to the control group will receive no-acupuncture treatment during the study. Baseline assessment will be conducted for all eligible participants. The participants who agree to accept acupuncture treatment will be allocated to treatment group, while those who refuse to accept acupuncture treatment will be allocated to control arm.

All acupuncture treatment sessions will be performed by two to three acupuncturists who are registered Chinese Medicine Practitioners in Hong Kong and have at least 3 years of clinical experience in acupuncture practice. Interventions will be conducted according to STRICTA and ICH-GCP guidelines. To ensure the consistency of skill of various acupuncturists, two to three training workshops will be provided to acupuncturists who have participated in the study prior to the commerce of the study. The acupuncture experts panel of School of Chinese Medicine, The Chinese University of Hong Kong, will provide technique training on the selection of acupuncture points and needling techniques. The workshops will be videotaped for education purpose.

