## 7. Manipulation Procedure

Sterile disposable stainless steel needles of various lengths and diameters will be used in the study. The standardized needling manipulation methods on different acupuncture points are described as follows: GB12, GB20 (a depth of 0.8–1.2 cun with the needle tip pointing towards the throat will be punctured, and needles will be rotated with reinforcing techniques); CV23 (about 1.0 cun towards the root of the tongue will be inserted obliquely, and mild lifting and thrusting technique will be applied for about 1 min); DU20 (at an angle of 30 degrees, angle to a depth of 0.5 to 0.8 cun will be inserted obliquely, and the needle will be rotated about 30 seconds before withdrawing the needle); LI4 (puncture perpendicularly for 0.5 to 1.0 cun, and apply for 30 seconds reinforcing technique with the lifting and thrusting movement); HT5 (a depth of 0.5 cun will be punctured perpendicularly, reinforcing technique with the lifting and thrusting movement will be applied for 30 seconds); Hangsang (a needle of 75 mm in length will be applied to prick the posterior wall of the throat at the depth of about 0.15 cun for 4 times without retaining the needle); Shanglianquan (a depth of 1.0–1.5 cun towards the root of the tongue will be inserted obliquely, and mild lifting and thrusting technique will be applied for 30 seconds); Lower 2/5 of the motor zone of scalp acupuncture (the needle will be inserted transversely at an angle of 15 degrees to the skin surface and push the needle to about 1.0 cun in depth, and twirling method will be applied for about 30 seconds); ST40 (the needle will be punctured perpendicularly for 1.5 cun, and reducing technique by lifting and thrusting the needle will be applied); LR3 (the needle will be inserted perpendicularly for 0.5–1.0 cun, and reducing techniques by lifting and thrusting the needle for 30 seconds will be applied) (Table 1).

The acupuncture treatment will be administered once every two days, three times a week, and the whole treatment period will last for 2 months. A total of 24 acupuncture treatment sessions will be carried out on each patient.

Participants who are allocated to nonacupuncture controlled group will receive routine care without acupuncture treatment.

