## 9. Secondary Outcomes

The secondary outcome measures include functional oral intake scale [21], swallow quality-of-life questionnaire in Chinese version [22], BMI [7], and adverse event report.

Functional oral intake scale, or known as swallow function scores, is a 7-point scale that describes the severity of swallowing dysfunction.

Swallow quality-of-life questionnaire in Chinese version consists of 12 items. The items covered all physical and psychosocial impact of the patients. Swallow quality-of-life questionnaire in Chinese version is chosen as secondary outcome because it is as sensitive, valid, and reliable as original version [22].

All adverse events as defined by the Ethics Committee will be fully recorded on the Adverse Event Page of the Case Report Form.

All functional oral intake scale, swallow quality-of-life questionnaire in Chinese version, and BMI will be assessed at baseline (before the intervention), the end of treatment (2 months after inclusion), and the end of follow-up period (2 months after treatment completion).

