Blinding is a crucial measure to assure the quality of the trial. All outcome assessor and statistician will be kept blind throughout the whole process. We will minimize the interaction between the patients and outcome assessors. Neither the RBHOMS assessor nor the staff who administer the questionnaire knows the group allocation of the participants.

One main limitation of this study is lack of randomization. Randomization is a key procedure to minimize the selection bias and ensure the comparability of all parameters between the intervention group and control group. However, concerning the timeframe and budget of our pilot study, nonrandomization approach will be utilized. To reduce the selection bias of our study, subjects will be recruited from different sources, including hospitals, speech therapy outpatient clinics, and Chinese medicine clinics. Moreover, all the prognostic factors and baseline characteristics of participants such as gender, age, occupation, life style, and onset time of stroke will be controlled in both acupuncture group and nonacupuncture control group. All data will be collected to examine the baseline comparability and explore the possible sources of dissimilarity and make proper statistical adjustment later.

As for all clinical trials, subject recruitment is one of the most critical factors for the trial's successful implementation. In our study, various venues and approaches will be utilized to augment the subject recruitment process. Free Chinese medicine consultation will be provided to control arm participants as an incentive. In addition, we will also hold promotional talks in the Chinese medicine clinics to facilitate the recruitment process. Moreover, we may also place advertisements on local newspapers and contact the stroke patients association to boost subject recruitment if recruitments from hospitals and Chinese medicine clinics turn out to be undesirable.

Nonetheless, most of potential subjects of this study are stroke sufferers. They always have other complications, such as immobility. In order to reduce the dropout rate and to enhance the compliance of patients, some treatment sessions may be conducted at affiliated mobile clinics.

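### The intention-to-treat rule covers every analysis without exception, so patients who agree to acupuncture but are never needled stay in the adverse event denominator and can dilute needling-related harm

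*Protocol article*

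**What the plan says.** Section 11 (Data Analysis) opens with a rule that has no exception: "All analyses will be conducted according to the intention-to-treat principle". It then provides for descriptive statistics on all analysed variables. It names tests for the primary outcome, the continuous variables and the swallow function scores, but none for adverse events.

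Safety is nevertheless within scope. The objective in section 2 is to "evaluate the effectiveness and safety of acupuncture", and section 9 lists "swallow quality-of-life questionnaire in Chinese version [22], BMI [7], and adverse event report" among the secondary outcomes.

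Section 5 (Intervention) defines membership of the acupuncture group: "The participants who agree to accept acupuncture treatment will be allocated to treatment group". Agreement decides the group, not receipt. The planned exposure is in section 7: "A total of 24 acupuncture treatment sessions will be carried out on each patient". Section 3.5 allows withdrawal for noncompliance and for unexpected serious side effects. Section 10 raises 60 per group to 70 to allow for 15% dropout while treatment is under way.

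**The concern.** For an effectiveness comparison, keeping every allocated patient in the group they joined usually errs on the cautious side. For harm caused by the procedure it works the other way. An event due to needling can occur only in someone who was needled. A patient who agreed and never attended adds one to the denominator and cannot add to the numerator, so for needling-specific events the rule can only lower the observed rate.

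The main argument for intention-to-treat, that it preserves a randomised comparison, is not available here, because the trial is nonrandomised by design. The rule therefore brings possible dilution of harm without that compensating benefit. Section 1 says the pilot is meant to provide evidence for a later full-scale trial, so its harm rates are likely to be carried forward.

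**Working it through.** **Inputs from the article**

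- 60 per group before inflation, 15% dropout allowance, 70 per group recruited (section 10).
- Acupuncture group defined by agreement (section 5).
- Intention-to-treat for all analyses (section 11).

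**Inputs that the article does not give (assumptions)**

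- f, the share of acceptors who are never needled: taken as 0 to 15%. The upper end assigns the whole dropout allowance to patients who never had a session.
- r, the event rate in needled patients, and r0, the event rate without needling: illustrative values.

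**Step 1. The plan's own figure.** 60 × 1.15 = 69, and 60 / 0.85 = 70.6, rounded up to 71. The stated 70 lies between the two, so it is reproduced to within rounding. In reverse, 70 × 0.85 = 59.5, or about 60 patients left if the full allowance is lost.

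**Step 2. Dilution.** The rate over all allocated patients is r × (1 − f) + r0 × f.

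For needling-specific events r0 = 0, so the reported rate is r × (1 − f) and the relative dilution is exactly f. With r = 10%:

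| f | Reported rate |
|---|---|
| 0% | 10.0% |
| 5% | 9.5% |
| 10% | 9.0% |
| 15% | 8.5% |

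As a count, 6 events among 60 needled patients are 6/60 = 10.0%. Over 70 allocated they are 6/70 = 8.6%. Here f = 10/70 = 14.3%, slightly below 15%. The number of events does not change.

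**Step 3. With background events.** Take r = 20%, r0 = 10%, f = 15%. The reported rate is 0.20 × 0.85 + 0.10 × 0.15 = 0.170 + 0.015 = 18.5%. The total rate falls by 1.5 points (7.5% relative). The excess over background falls from 10.0 to 8.5 points, again 15% relative.

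**Step 4. No events of a given kind.** The one-sided 95% upper limit is 1 − 0.05^(1/n).

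- n = 70: 1 − 0.05^(1/70) = 4.2%.
- n = 60: 1 − 0.05^(1/60) = 4.9%.

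At the extreme of the range, the limit looks about 0.7 points tighter than the exposed patients support. The article itself states no confidence limit for adverse events; these figures only illustrate the size.

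**The case against.** The strongest reply is that section 11 specifies no adverse event analysis for the rule to distort. Every test it names concerns an effectiveness outcome, and a condensed article may leave the safety set to the full protocol or the analysis plan. That is fair as far as it goes: the lack of a safety set definition is not the point here. The point is the unqualified opening sentence. A descriptive event rate also needs a denominator, and that sentence supplies one.

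A second reply is that few acceptors are likely to go untreated, since patients choose their own group and the 15% allowance is for losses during treatment, many of whom will already have been needled. This stands. It is why 15% is an upper bound and why nil is possible.

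A third reply is that intention-to-treat guards against losing patients withdrawn for serious side effects. It does, but anyone harmed by needling has had at least one session, so a set based on treatment received keeps that patient as well.

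A reader might infer several stronger points that the article does not support:

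- *That patients who stop after a few sessions are an intention-to-treat problem.* They would also be in a set defined by at least one session. Their limited exposure is a separate matter, addressed by showing sessions delivered.
- *That the protocol expects non-starters.* Section 12 says of the patients that "They always have other complications, such as immobility", but it goes on to offer mobile clinics as a way to limit dropout. It does not predict that acceptors will fail to start.
- *That controls who take up acupuncture will be counted as unexposed.* Controls are people who refused acupuncture and are to receive routine care without it. Nothing in the article indicates crossover.
- *That the plan relies on a particular upper limit or on planned sessions as a denominator.* It states neither.

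**Conclusion.** The point holds in limited form. Taken literally, the blanket rule applies to adverse events and keeps never-needled acceptors in the acupuncture denominator. For needling-specific events this can only lower the rate.

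The relative dilution equals the never-needled share. That share is unknown, so the effect runs from nil to at most about 15%. The upper end rests on the assumption that the whole dropout allowance was never needled, which is unlikely because the allowance concerns losses during treatment. A conclusion that acupuncture will be made to look safer than it is would go too far: the documents support only that it could be, by a modest amount. This is a minor wording point, worth correcting because the correction is so cheap.

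**What to change.** In section 11, limit the intention-to-treat sentence to effectiveness outcomes and add a sentence on harms. Possible wording: *Effectiveness outcomes are analysed by intention-to-treat. Adverse events are summarised by treatment received, where the acupuncture group is every participant who had at least one session; the number of sessions delivered and the counts for all allocated participants are shown alongside.*

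The cost is one or two sentences and one extra table. No new patients or visits are needed, although the number of sessions each patient received must be recorded. No randomised comparison is given up, since there is none. The only downside is that the reported harm rate may be slightly higher. If every acceptor has at least one session and no control is needled, the two summaries agree and nothing is lost.

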## 3. Methods and Design

### 3.1. Study Design

This is a multicenter, pragmatic clinical trial comparing real acupuncture intervention with no acupuncture to evaluate the treatment effects of acupuncture on the outpatient population of poststroke dysphagia. Owing to the characteristic of poststroke dysphagia patient and the nature of acupuncture, it is not feasible to implement the sham acupuncture in this study. The patients in acupuncture group and no-acupuncture control group will be in 1 : 1 allocation ratio. Subjects who are eligible in study and willing to accept acupuncture will be allocated to intervention group, while subjects eligible in study but refuse to have acupuncture treatment will be put on the no-acupuncture control arm. In the real acupuncture group, patients will receive acupuncture intervention in addition to conventional treatment. Real acupuncture group is defined as the group in the study that receives a series of sessions of acupuncture treatment which is being tested. The study will be conducted in several Chinese medicine clinics including The Pok Oi Hospital, The Chinese University of Hong Kong Clinical Center for Teaching and Research in Chinese Medicine (Shatin and Yuen Long), and The Yan Oi Tong, The Chinese University of Hong Kong Clinical Center for Teaching and Research in Chinese Medicine (Tuen Mun). Acupuncture treatment may also be conducted at the affiliated mobile clinics of these centers. This project is approved by both the Joint Chinese University of Hong Kong-New Territories East Cluster Clinical Research Ethics Committee (CRE-2012.236-T) and New Territories West Cluster Clinical Research Ethics Committee (NTWC/CREC/1281/14). Written informed consent is obtained from each participant. The study will be conducted according to ICH-GCP Guidelines. The study design is described in Figure 1.

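### Arms are formed by patient choice, but the only test named for the primary outcome is an unadjusted chi-square, with adjustment deferred until baseline comparability has been examined

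*Protocol article*

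**What the plan says.** Protocol article, section 3.1 (Study Design) forms the arms by preference alone: "Subjects who are eligible in study and willing to accept acupuncture will be allocated to intervention group". Those who decline it become the controls. Section 5 (Intervention) repeats this. The two groups "will be in 1 : 1 allocation ratio", which fixes their relative size and not their comparability.

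Section 10 sizes the trial on the proportion of patients at RBHOMS stage D. Section 11 (Data Analysis) gives one test for it: "For the primary outcome, chi square test will be used". The only model-based analysis in that section is exploratory and open as to covariates: "The possible relationship between some baseline data and main outcomes will be explored using multivariable analysis".

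Section 12 (Discussion) names the lack of randomisation as a main limitation. It then makes three statements about handling it:

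- Prognostic factors and baseline characteristics, with gender, age, occupation, life style and onset time of stroke as examples, are to be controlled in both groups.
- Baseline data will be collected to examine comparability, "explore the possible sources of dissimilarity and make proper statistical adjustment later".
- Varied recruitment is itself a remedy: "To reduce the selection bias of our study, subjects will be recruited from different sources".

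**The concern.** A chi-square on two raw proportions answers the treatment question only if the arms would have had the same stage D rate without acupuncture. Randomisation would justify that assumption; acceptance and refusal do not. The entry criteria leave wide room for prognostic difference: RBHOMS from 2 to 8, up to 12 months after stroke, and either ischaemic or haemorrhagic stroke (section 3.3). The Background also notes that dysphagia resolves naturally in many patients early after stroke.

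The assurance that prognostic factors are controlled is not matched by any matching, stratification or adjusted primary model in sections 3 to 11. Adjustment is promised, but its content is to be settled after the imbalances are visible, and it is not attached to the primary test. A significant primary result could then reflect who chose acupuncture, and a null result could conceal a benefit. Either would undermine the stated objective of evaluating effectiveness.

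**Working it through.** **The plan's own figure.** Section 10 gives 60 per arm for a 20-point difference, with 5% error and 80% power. The control rate is not stated, so 60 cannot be reproduced uniquely. The usual two-sided pooled formula gives 57 per arm for 8% vs 28%, 62 for 10% vs 30%, and 97 for 40% vs 60%. That is a separate matter. Here 60 per arm is simply taken as the number analysed.

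**Set-up (assumed, because the documents give no rates).** There is no treatment effect and one binary prognostic factor. Stage D rates are pH and pL with and without the favourable factor. Its prevalence is fA among acceptors and fC among refusers.

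- Expected proportions: a = fA·pH + (1 − fA)·pL and c = fC·pH + (1 − fC)·pL.
- Spurious difference: d = a − c.
- Rejection probability: Φ((d − 1.96·s0)/s1) + Φ((−d − 1.96·s0)/s1), where s0 = √(2·m(1 − m)/60), m = (a + c)/2, and s1 = √((a(1 − a) + c(1 − c))/60).

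**One case in full.** Take pH = 0.6, pL = 0.2, fA = 0.6, fC = 0.4.

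- a = 0.36 + 0.08 = 0.44; c = 0.24 + 0.12 = 0.36; d = 0.08.
- m = 0.40; s0 = √(0.48/60) = 0.0894; s1 = √(0.4768/60) = 0.0891.
- First term: Φ((0.08 − 0.1753)/0.0891) = Φ(−1.07) ≈ 0.142. Second term ≈ 0.002. The total is about 14.5%.

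**Range (spurious difference in points; false-positive rate).**

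| Prevalence, acceptors/refusers | 60% vs 30% | 60% vs 20% | 70% vs 20% |
|---|---|---|---|
| 50/50 | 0; 5.0% | 0; 5.0% | 0; 5.0% |
| 55/45 | 3; 6.2% | 4; 7.3% | 5; 8.5% |
| 60/40 | 6; 10.1% | 8; 14.5% | 10; 19.5% |
| 65/35 | 9; 16.7% | 12; 26.7% | 15; 37.8% |
| 70/30 | 12; 26.0% | 16; 43.1% | 20; 59.8% |

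Columns are the assumed stage D rates by prognosis. In the most extreme cell the bias equals the 20-point target effect. With the prevalences reversed, the same differences count against acupuncture. If effects add, an 8-point bias in that direction would reduce a true 20-point difference to about 12.

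**Does adjustment help?** In a simulation of the 60% vs 20% column (4,000 runs per setting), the unadjusted chi-square rejected in 5.0%, 14.4%, 28.8% and 44.7% of runs at 50/50, 60/40, 65/35 and 70/30. A Cochran–Mantel–Haenszel test stratified on the factor stayed between 4.8% and 5.1%. This shows correction for a measured factor only.

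**Baseline RBHOMS.** Section 3.3 admits levels 2–8; section 8 defines stage D as levels 8–10. A patient entering at level 8 already meets the endpoint. Before any treatment, the arms therefore differ in stage D by exactly the difference in their shares of level-8 entrants. A 10-point difference in those shares is a 10-point difference in the endpoint at baseline.

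**Precision cost if source does track arm (speculative).** Suppose half of recruits come from Chinese medicine clinics with 90% acceptance and half from speech therapy clinics with 40%. The Chinese medicine share is then 0.45/0.65 = 69% of acceptors and 0.05/0.35 = 14% of refusers. With equal arms the arm–source correlation is 0.5495 × 0.5/√(0.4176 × 0.5824) ≈ 0.56. The variance inflation is 1/(1 − 0.31) ≈ 1.45, so 60 per arm carries the information of about 60/1.45 ≈ 41. These acceptance rates imply a 65:35 split rather than the planned 1:1, so this illustrates the cost and does not predict it.

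**The case against.** The protocol is open about its main weakness, calls itself a pilot for a later full-scale trial, and commits to statistical adjustment. In the Discussion it is the search for sources of dissimilarity that is exploratory; the adjustment is a separate promise. A condensed article may leave the covariate list and model form to an analysis plan, and their absence is not the fault here. All of this stands. It does not rescue the primary test: section 11 states which test is used, that test is unadjusted, and the promised adjustment is neither tied to it nor settled before the imbalance is seen.

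Three stronger readings are tempting, and the documents do not support them:

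- **That the arms draw on different recruitment sources.** The text describes one pool for the whole study: "subjects will be recruited from different sources, including hospitals, speech therapy outpatient clinics, and Chinese medicine clinics". Speech therapy patients may accept or refuse, and control participants are offered free Chinese medicine consultation, which could draw patients inclined to Chinese medicine into the control arm. Source may track arm, but nothing says that it does.
- **That baseline RBHOMS is left out of the factors to be controlled.** The Discussion's list is illustrative, and RBHOMS is measured at baseline (section 8). Not being named as an example is not exclusion.
- **That imbalance will produce a false benefit.** Its size and direction are unknown. Acceptors could be more severely affected, which would mask a benefit.

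**Conclusion.** The point holds in this form: the primary test as written is unadjusted in a trial whose arms are self-selected, and the stated intention to control prognostic factors is not carried into that test. Its nominal 5% error is valid only if acceptors and refusers share the same prognosis. Under the assumed imbalances, with 60 per arm and no effect, the error is 6–9% for a mild 55/45 imbalance, 10–20% at 60/40 and 26–60% at 70/30. These figures rest on assumed stage D rates and prevalences, and show what can happen rather than what will.

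Recruiting from several sources may broaden the sample, but it does not in itself balance arms that patients choose, so the claim that it reduces selection bias is unsupported. A reader might infer that it worsens the bias; that too goes beyond the text.

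**What to change.** Before outcome data are seen, amend section 11 as follows:

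- Keep the stage D proportion, on which the trial is sized, as the primary endpoint, at one time point named in advance (RBHOMS is measured after treatment at month 2 and month 4).
- Make the primary analysis a prespecified adjusted comparison, for example logistic regression reported as a standardised risk difference, or propensity-score weighting.
- Fix the covariates: baseline RBHOMS, time since stroke, age, sex, stroke type and recruitment source.
- Report the chi-square as unadjusted and supportive.

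In section 12, remove the claim that multiple sources reduce selection bias, and align the statement about controlling prognostic factors with the adjusted analysis. Word the conclusion as an adjusted association with possible residual confounding.

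The cost is mainly wording, plus one extra recorded field (recruitment source); baseline RBHOMS is already collected and no extra visits are needed. It is not free statistically. Covariates correlated with arm, source in particular, reduce precision, so power at the planned size may fall. Adjustment cannot remove unmeasured differences between acceptors and refusers.
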